### Sample size

The primary outcome indicator adopted in this study is exercise adherence. The sample size was calculated using the sample size estimation formula for multiple means in randomized controlled trials, accounting for a 20% dropout rate, resulting in a final sample size of 100 subjects. The sample size calculation was determined using PASS 2021 software.

### Randomization, allocation, and blinding mechanisms

This study employs a computer-generated simple randomization method. Before the trial, a researcher will use computer software to randomly generate a randomization number list, allocating patients to four groups in a 1:1:1:1 ratio: Group A (gain-narrative framed message), Group B (loss-narrative framed message), Group C (gain-framed non-narrative message), and Group D (loss-framed non-narrative message). The generated random number list will be stored in a sealed envelope until the randomization process is completed. The researcher responsible for generating the random sequence will not participate in the patient recruitment process.

This study will be blinded to the participants, who received the educational video via WeChat. During this process, patients will not be aware of which message-framed video they received. Meanwhile, the video interventions in the four groups will be designed to mask the content of the different screens through similar designs (such as textual descriptions, animations combined with case presentations), and the researchers will personalize reminders and instructions based on patients’ responses during the experiment, and will process the feedback through a standardized template to avoid disclosing the group characteristics and to ensure the effectiveness of the interventions. Unblinding may be performed during the trial when essential to ensure participant safety or to facilitate necessary therapeutic adjustments in the event of a serious adverse event to minimize any potential impact on study outcomes, as reported by the participant or as assessed by the study investigators and the treating physician. If unblinding is required during the trial, the reasons, timing, participant-related information, and the corresponding decision-making process will be fully documented and archived. All unblinding procedures will adhere to ethical standards.

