### Data statistics and analysis

Statistical analysis of the data will be performed using SPSS 25.0 and R 4.3.2 software. All statistical analyzes will be conducted using two-sided tests, with a significance level set at *p* < 0.05. Continuous variables will be described using mean ± standard deviation, while categorical variables will be expressed as frequency (n) and percentage (%). For intergroup comparisons of baseline data: continuous variables that follow a normal distribution will be compared using one-way analysis of variance (ANOVA); those that do not follow a normal distribution will be compared using the Kruskal–Wallis nonparametric test. Categorical variables will be compared using the chi-square test or Fisher’s exact test, as appropriate.

To comprehensively analyze changes in outcome indicators across different groups and time points following the intervention, data will be analyzed using a linear mixed-effects model (LMM). The gain-loss framing, narrative framing, and time will be included as fixed effects, while individual study participants will be included as random effects to account for individual variability. The LMM model will be constructed to assess the main effects of the gain-loss framing, narrative framing, and time, as well as their interaction effects. If the interaction effects are significant, further analysis of the simple effects of the message framing and time will be conducted to explore the impact of the intervention on outcome indicators at different time points. If interaction effects are not significant but main effects are, Tukey’s HSD *post hoc* comparison analysis will be further conducted to explore the independent effects of different message framing and time points on outcome indicators. The LMM model uses maximum likelihood estimation and is able to fit the model efficiently using all available data containing missing values, and is therefore robust to missing data.

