### Implementation challenges and solutions

During implementation, the study faced major challenges, including high patient dropout rates and standardization of intervention content. To address these issues, the research team took the following measures: improving patient participation through WeChat red envelope incentives and regular follow-ups; developing standardized intervention videos and test questions to ensure consistency of content; and providing uniform training to researchers to reduce operational bias. In addition, the study further controlled for confounding factors through stratified Randomization and baseline data balancing.

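### The methods specify simple randomisation but the discussion claims stratified randomisation controlled confounding; both cannot be true, and under the methods text that protection does not exist

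*Protocol article*

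**What the plan says.** The section on randomization, allocation and blinding gives the operative description: "This study employs a computer-generated simple randomization method". It adds that a number list will be generated by software before the trial, "allocating patients to four groups in a 1:1:1:1 ratio". It mentions no strata, blocks or minimisation.

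The discussion, under implementation challenges and solutions, lists the measures taken against practical difficulties and closes with: "In addition, the study further controlled for confounding factors through stratified Randomization and baseline data balancing". No stratification factor and no balancing procedure is named there or elsewhere in the article.

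The data statistics and analysis section gives gain-loss framing, narrative framing and time as the fixed effects of the linear mixed model, with participant as a random effect. No stratification factor or other baseline prognostic covariate is listed. On size, the sample size section reports "accounting for a 20% dropout rate" and "resulting in a final sample size of 100 subjects".

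**The concern.** These are two positive statements about the same design feature, and they exclude each other. A list made by simple randomisation ignores patient characteristics. A stratified list is made separately within levels of named characteristics. A reader cannot tell which list will be, or was, used.

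Three things depend on the answer. The first is whether the stated control of confounding exists at all, since the discussion offers it as a strength. The second is the analysis: factors used to stratify allocation normally belong in the model, and the model described has none. The third is what arm sizes to expect, since simple randomisation of 100 patients into four arms does not hold each arm near 25.

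**Working it through.** **Inputs.** Total of 100 patients and 20% dropout (sample size section); four arms at 1:1:1:1 (randomisation section); fixed effects as listed in the analysis section, with their interactions.

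**The plan's own figure.** The effect size, standard deviation and power behind the 100 are not printed in the article, so the calculation cannot be reproduced. Only the dropout step can be checked: 80 / (1 − 0.20) = 100, which corresponds to 20 evaluable patients per arm. Nothing below depends on the unprinted inputs.

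**Step 1: compatibility.**

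| | Randomisation section | Implementation section |
|---|---|---|
| Method | Simple | Stratified |
| Strata | None by definition | Required, none named |
| Baseline factors balanced by design | None | The stratification factors |

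No reading of a single list satisfies both columns. The baseline comparisons planned in the analysis section (ANOVA, Kruskal–Wallis, chi-square, Fisher) do not bridge the gap, because testing for differences does not remove them.

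**Step 2: arm sizes if the list is unrestricted.** Arm sizes then follow a multinomial distribution with N = 100 and probability 0.25 for each arm.

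- SD of one arm: √(100 × 0.25 × 0.75) = 4.33; 95% range 17 to 34.
- P(exactly 25 in every arm) = 100! / (25!)⁴ / 4¹⁰⁰ = 0.0010, or 0.1%.
- P(largest minus smallest arm ≥ 10) = 54%; P(≥ 15) = 17%.
- P(smallest arm ≤ 18) = 25%.

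**Step 3: cost in precision.** Write A, B, C, D for the four arm means. With the interaction in the model, the contrasts are:

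- gain-loss main effect: ½[(A − B) + (C − D)]
- narrative main effect: ½[(A − C) + (B − D)]
- interaction: (A − B) − (C − D)

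The variance is (σ²/4) Σ(1/nᵢ) for each main effect and σ² Σ(1/nᵢ) for the interaction. Relative to equal arms, all three are therefore inflated by the same ratio, Σ(1/nᵢ) / (4/25).

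- Example, arms of 25, 32, 18 and 25: (0.0400 + 0.03125 + 0.05556 + 0.0400) / 0.16 = 0.16681 / 0.16 = 1.043.
- Approximate mean: 1 + 18.75/25² = 1.03. Over the full multinomial distribution the mean is also 1.03.
- 95th percentile: 1.09.

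If the interaction were left out, so that each main effect compared the two pooled margins, the mean efficiency would be 99.0%, a loss of about 1%.

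These ratios use randomised numbers. Dropout at the same rate in every arm leaves the ratio unchanged.

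**The case against.** The strongest reply is that this is one loose sentence in a discussion, set against a clear methods section, and that little follows from it numerically. Much of that stands. Simple randomisation gives unbiased comparisons, and chance imbalance is already part of the sampling error that the tests allow for. A reader might infer that the trial is confounded or its type I error inflated; the documents do not support that.

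Four other tempting inferences also fail.

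- **That unequal arms damage the interaction most.** With the interaction fitted, Step 3 shows the same proportional cost for all three contrasts. The lower power for interaction is a general feature of factorial trials.
- **That 1:1:1:1 contradicts simple randomisation.** The ratio can be read as equal allocation probability, which simple randomisation satisfies. The pre-generated list might even hold exactly 25 per arm, in which case Step 2 does not apply.
- **That chance imbalance in a prognostic factor passes undiminished into the framing effects.** The outcome is measured at baseline and the model includes time, so a factor that only shifts a patient's general level largely drops out of the framing-by-time contrasts. Factors that predict change, or an effect averaged over all time points, remain exposed. Such imbalance also arises under unstratified blocks, so it cannot be charged to simple randomisation alone.
- **That missing strata or block sizes are themselves an error.** The article says that the full protocol and analysis plan are in the registry, and those details may be there.

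What does not fall is the contradiction. Condensing a protocol into an article can explain missing detail, but not the naming of two different methods. An unseen document could show which statement is right; it could not make both right.

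**Conclusion.** The two descriptions of allocation are incompatible, and the claim that confounding was controlled by stratification is unsupported if the randomisation section is correct. This should be fixed. The defect is an unresolved and possibly false statement of a core design feature, not a loss of validity.

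If allocation is truly unrestricted, arm sizes will often be visibly unequal (a gap of 10 or more in about 54% of trials). The variance cost is about 3% on average and about 9% or more in 1 trial in 20. These figures assume independent allocation with probability one quarter per arm and the same residual variance in each arm. They do not apply if the list was built with fixed arm totals.

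The reference to balancing baseline data is too vague to judge. A reader might take it to mean manipulation after allocation, but the article does not say so, and it may only be a loose reference to the baseline comparisons. Neither that nor the comparisons themselves would control confounding.

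**What to change.** State one procedure in both sections and make the analysis model match it. Which branch applies depends on whether allocation has begun, which the article does not make clear.

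- **If allocation has not started:** use permuted blocks of varying size, concealed from recruiters, stratified by at most one or two factors already collected. History of acute myocardial infarction, in the listed baseline disease data, is an example. Add those factors to the mixed model as fixed effects. Blocks of 4 without strata would give exactly 25 per arm; with two strata of roughly equal size (an assumption for illustration), every arm would hold 24 to 26. The cost is a new computer-generated list, a few words of text and slight predictability, which varying block sizes and concealment keep small. A factor that is only an eligibility condition, such as caregiver help with WeChat, would first have to be added to the baseline form.
- **If allocation was simple:** delete the claim of stratification and baseline balancing from the discussion, say that realised arm sizes may differ, and pre-specify adjustment for a short list of collected baseline prognostic factors in the mixed model. The cost is a text correction and a few degrees of freedom. The list should be fixed before outcome data are examined.
- **If allocation was in fact stratified:** correct the randomisation section, name the factors and add them to the model.

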### Interventions

The intervention content of this study will be based on the exercise rehabilitation education program. On the day of discharge, researchers will select a quiet private departmental meeting room and use a time-slot booking system to ensure that the four participant groups do not overlap. We will explain the purpose, methods and procedures of the intervention to patients face-to-face and implement the first intervention. Educational videos will be sent to participants via WeChat for viewing and learning, serving as the primary form of the intervention. Participants will be guided through the video-viewing process, and after viewing, they will be asked questions regarding the basic content presented in the video. If the patients are unable to recall the content, the video will be replayed until the patients indicate they understand the content. During the viewing period, any questions raised by the patients will be promptly addressed.

In weeks 1, 2 and 3 after discharge, the researcher will remind patients to watch the video after sending the corresponding study content and video every week. After viewing, participants will be invited to answer two brief questions related to the video content. The researcher will also maintain continuous communication with participants and will promptly address any questions raised during the study period. After completing each video study and test, patients will be praised and encouraged via WeChat to improve adherence. The four groups will receive different contents of short educational videos, but the mode, timing, and frequency of video delivery and question prompts are the same across groups. The health education content provided by medical staff during hospitalization and in routine post-discharge follow-up is also identical. In this study, scientifically validated exercise instruction videos will be provided, clearly listing contraindicated exercises and emergency stop signals. We will inform patients of the procedures to be followed in case of discomfort during exercise to ensure patient safety. The process of intervention implementation can be seen in Table 2.

**Table 2 tab2:** Process of implementation of the exercise rehabilitation education program.

Intervention time	Video theme	Frame				Intervention implementation
		Group A	Group B	Group C	Group D	
On the day of discharge	Post-PCI exercise rehabilitation education	Frameless	Frameless	Frameless	Frameless	Face-to-face, WeChat
1 week after discharge	Aerobic exercise guidance	Gain frame	Loss frame	Gain frame	Loss frame	WeChat
2 Weeks after discharge	Resistance exercise guidance	Gain frame	Loss frame	Gain frame	Loss frame	WeChat
3 Weeks after discharge	Flexibility exercise guidance	Gain-narrative frame	Loss-narrative frame	Gain frame	Loss frame	WeChat

During the intervention period, patients in all four groups can continue to receive their regular medical treatment and rehabilitation management (e.g., medication, dietary adjustments, psychological support, etc.), which are assessed to be compatible with the intervention content of this trial and are not expected to affect the effectiveness of the intervention. If patients need to receive other treatments (e.g., surgery, emergency treatment, etc.) or adjust their routine treatment due to health problems during the trial period, the research team will assess whether these treatments affect the efficacy and credibility of the findings of the trial and decide whether participants can continue to participate in the study. In addition, any additional treatments or medications other than routine treatment will be reported to the research team in advance and will be evaluated by the research team as appropriate to ensure that they do not adversely affect the trial intervention.

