## Methods

### Study design

This is a two-phase study:

*Phase 1*: We will develop an exercise rehabilitation education program for post-PCI patients based on the message framing effect through qualitative needs assessment, evidence synthesis, and expert consensus.*Phase 2*: We will conduct a prospective, parallel-controlled, single-blind randomized controlled trial using a 2 (gain vs. loss framing) × 2 (narrative vs. non-narrative framing) factorial design to implement the exercise rehabilitation education program, comprising four groups: Group A (gain-narrative framed message), Group B (loss-narrative framed message), Group C (gain-framed non-narrative message), and Group D (loss-framed non-narrative message). This phase includes a 3-week intervention period and a 3-month follow-up period. The study design is shown in Figure 1.

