### Final draft

Unlike traditional educational formats, this study will innovatively combine the theory of message framing effect, centring on the knowledge of exercise rehabilitation of aerobic exercise, resistance training and flexibility training, and present each exercise from the perspective of the benefits of exercise and the risks associated with inactivity. Real-life case studies will also be incorporated, resulting in the final draft of the rehabilitation education program for post-PCI patients. Through the combination of gain-loss framing and narrative framing, four groups of differentiated educational materials will be developed. The gain framing will emphasize the positive outcomes and benefits patients can achieve through exercise rehabilitation, such as improved cardiac function, reduced risk of cardiovascular events, enhanced physical strength, and improved quality of life. The loss framing will highlight the negative consequences and potential losses patients may face if they do not follow exercise rehabilitation recommendations. Additionally, by using specific patient stories of exercise rehabilitation and employing emotional narratives, the narrative framing will enhance patients’ emotional resonance and understanding, thereby better promoting the implementation of exercise rehabilitation education. Considering that most patients with coronary heart disease are older adults and that many experience age-related visual impairment, which makes reading and understanding text difficult, they tend to prefer receiving exercise rehabilitation education messages in video format for easier comprehension and learning. Based on the findings of the literature review and qualitative interviews, animated video presentations are therefore incorporated in addition to the text-based exercise rehabilitation education program. The videos will be designed to present the textual content of the educational messages in bold characters, with appropriate pictures, animations, voice-overs and background music to enhance the readability and interest of the videos, and the length of each video will be controlled to be within the range of 3–6 min.

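### Table 2 separates the narrative from the non-narrative arms by one week-3 flexibility video only, so the narrative main effect and the interaction are narrower than the 2×2 design implies

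*Protocol article*

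**What the plan says.** Under Study design, Phase 2 is a "2 (gain vs. loss framing) × 2 (narrative vs. non-narrative framing) factorial design to implement the exercise rehabilitation education program". The arms are "Group A (gain-narrative framed message), Group B (loss-narrative framed message), Group C (gain-framed non-narrative message), and Group D (loss-framed non-narrative message", and the section on randomization and blinding repeats these labels. Under Final draft (Phase 1), the article says: "Through the combination of gain-loss framing and narrative framing, four groups of differentiated educational materials will be developed". That section describes the narrative frame as patient stories told with emotional content.

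The schedule is in Table 2 (Interventions). The discharge video is frameless in every arm. The week-1 video ("Aerobic exercise guidance") and the week-2 video ("Resistance exercise guidance") are gain-framed for A and C and loss-framed for B and D. Only in week 3, for flexibility exercise, does A receive the "Gain-narrative frame" and B its loss counterpart; C and D stay with plain gain and loss frames.

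Under Data statistics and analysis, the mixed model estimates main effects of gain-loss framing, narrative framing and time, and their interactions. Under Design justification and constraints, the design is credited with showing whether the two factors reinforce, oppose or act separately from each other. On masking, the videos of the four groups are meant to "mask the content of the different screens through similar designs (such as textual descriptions, animations combined with case presentations").

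**The concern.** The arm labels and the analysis lead a reader to expect narrative framing to be a property of the whole framed programme in A and B. The schedule confines it to one video, on one exercise type, in the last session. The article neither mentions nor explains this.

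Combining the two framings is what the article presents as its main novelty. If the trial runs as Table 2 shows and reports a narrative effect, or none, under the current labels, the conclusion will cover narrative framing of exercise education in general. The trial will have tested something much smaller. No analysis can repair this later, because the contrast is set by what patients were shown.

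A secondary uncertainty is that case presentations are named as a design feature common to the four groups, while patient stories are what defines the narrative frame. The text does not say how the two differ.

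**Working it through.** The article gives no figure for narrative exposure, so there is nothing to reproduce. The check is a count of the cells of Table 2, whose rows are complete in the text.

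| Video | A | B | C | D | A v C, B v D (narrative) | A v B, C v D (gain-loss) |
|---|---|---|---|---|---|---|
| Discharge, general education | none | none | none | none | same | same |
| Week 1, aerobic | gain | loss | gain | loss | same | differ |
| Week 2, resistance | gain | loss | gain | loss | same | differ |
| Week 3, flexibility | gain + narrative | loss + narrative | gain | loss | differ | differ |

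**Count**
- Narrative contrast: 1 of 4 videos, or 1 of 3 framed videos.
- Gain-loss contrast: 3 of 4 videos, or 3 of 3 framed videos.

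**What the model terms then mean.** Write A to D for the arm means at a given follow-up.
- Narrative main effect = [(A − C) + (B − D)] / 2.
- Gain-loss × narrative interaction = (A − C) − (B − D).

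By the table, A − C is the effect of making the week-3 flexibility video narrative within a gain-framed programme. B − D is the same effect within a loss-framed programme. The main effect is the average of these two single-video effects. The interaction asks only whether that one video works differently in a gain-framed and a loss-framed programme.

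**What cannot be separated.** Narrative occurs in A and B only with the flexibility topic and only in week 3. No term can distinguish narrative framing as such from narrative framing of flexibility advice in the final session. Nothing can be said about narrative framing of aerobic or resistance guidance. The primary outcome, as described, is a total exercise-adherence score with no restriction to flexibility exercise. A patient in A or B who stops before week 3 has, by the table, had the same programme as C or D.

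**The case against.** Several counter-arguments have weight.

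- **The contrast is randomised and valid.** This stands. The issue is what the contrast estimates, not bias.
- **Table 2 may be misprinted for weeks 1 and 2, and the article condenses a fuller protocol.** This is possible and the article does not settle it. If so, the schedule is misstated and still needs correcting, though the remedy is then editorial.
- **The Final draft section does not promise narrative in every session.** Correct. It ties each exercise to benefits and risks, and adds real cases without saying where they go. Four different sets of material also exist under Table 2. A reader might infer a direct contradiction with that section, but its wording does not support one. The conflict is with the arm labels and with the use made of the factor in the analysis and discussion.
- **Case presentations need not be patient-story narratives.** Correct. A reader might infer that C and D receive the narrative frame. The phrase is a loose list of examples, and Table 2 gives those arms no narrative frame. Contamination is only a possibility, and the feature serves participant masking.
- **How much narrative to deliver is a design choice.** This also stands, but a deliberate choice of one video must be named as such in the factor and the conclusions.

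**Conclusion.** The point holds on the cell count alone. As scheduled, the narrative factor is one narrative flexibility video in week 3 versus none: 1 of 3 framed videos, against 3 of 3 for gain versus loss. A positive result would support a statement about that video. A null would be uninformative about narrative framing in general. The gain-loss factor is present in every framed video and is not affected in this way. The verdict assumes that Table 2 lists the intended content, which the sponsor must confirm.

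Three stronger readings are not supported:
- **A stated loss of power.** The article gives no effect size, standard deviation or power, and nothing on how effect depends on the number of narrative videos. Any such figure would rest wholly on assumptions.
- **A fixed share of viewing time.** Videos may last 3 to 6 minutes each. With four videos the narrative one could take from 3/(3 + 18) = 14% to 6/(6 + 9) = 40% of the total.
- **An invalid comparison of the sizes of the two factors.** The article plans main effects and an interaction; it does not propose to rank the factors.

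**What to change.** Reconcile Table 2 with the arm definitions, by one of two routes.

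1. **Narrative is meant to run through all framed videos.** Correct the week-1 and week-2 cells for A and B. If those videos exist, this is an editorial correction. If they do not, up to four new versions are needed (two topics × two frames). That is new content for a programme built through expert consultation and patient try-out, and it needs an ethics amendment under the article's own rule for significant changes.
2. **Table 2 is right.** Restate the narrative factor, the interaction, the objective and the conclusions as the effect of adding one narrative flexibility video in week 3 to a gain- or loss-framed programme. Make no claim about narrative framing in general. The cost is wording and a narrower conclusion.

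Under either route, add a sentence to the blinding section stating that any case presentations shared across arms do not carry the patient-story narrative into C and D. The masking feature itself need not be removed.
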